The baseline covariate assessment period for all measures will start 180 days before cohort entry and will stretch up to and include the day of cohort entry with the following exceptions: (1) We will assess age, sex, race, region, year of cohort entry, and index prescription by a pulmonologist only on the day of cohort entry; (2) We will assess the presence of any prior asthma diagnosis using all available data and stretching up to (and including) the day of cohort entry. Diagnosis based covariates will be defined using any care setting and any diagnosis position unless otherwise specified. All codes for these variables are provided in Appendix Table 3, “Covariates.” The variable names are as listed below in Table 1. All variables listed below will be included in our propensity score model. We will use a missing indicator in our propensity score model in the case that data are missing for any covariates.

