**Table 1: Patient characteristics**

| **Characteristic** |
| --- |
|  |
| **Demographics** |
| Age |
| Female |
| Race |
| Region |
| **Year of cohort entry** |
| **Baseline lung disease** |
| Moderate COPD exacerbations |
| Severe COPD exacerbations |
| Total COPD exacerbations (moderate or severe) |
| SABA fills |
| SAMA fills |
| SAMA-SABA fills |
| Pneumonia hospitalizations |
| Respiratory antibiotic fills^b^ |
| Prior diagnosis of asthma (all available data) |
| Claim for home oxygen or oxygen equipment |
| CPAP/BiPAP |
| Spirometry |
| Index prescription by pulmonologist |
| Smoking |
| Pulmonary rehabilitation |
| LAMA |
| LABA |
| ICS |
| LAMA-LABA |
| ICS-LAMA-LABA |
| Chronic azithromycin |
| Roflumilast |
| Chronic prednisone |
| **Events within 30 days of cohort entry** |
| Moderate or severe COPD exacerbations |
| Respiratory antibiotic fill^b^ |
| **Other co-morbidities** |
| Combined comorbidity index |
| Frailty score |
| Obstructive sleep apnea |
| Hypertension |
| Diabetes |
| Obesity |
| Coronary artery disease |
| Peripheral vascular disease |
| Venous thromboembolic disease (DVT or PE) |
| Congestive heart failure |
| GERD |
| Renal failure |
| Osteoporosis |
| Dementia/other neurologic disease |
| Malignancy, non-metastatic |
| Metastatic solid organ malignancy |
| Anxiety disorder |
| Depression |
| **Healthcare utilization in baseline period** |
| Emergency department visits |
| Hospitalizations |
| 90-day readmissions |
| Office visits |
| Pulmonologist visits |
| Prescription drug claims |
| BMP or CMP |
| CBC with differential ordered |
| Electrocardiogram |
| Echocardiogram |
| CT scan |
| Bronchoscopy |
| Colonoscopy |
| Mammography |
| Bone-mineral density scan |
| Influenza vaccination |
| **Non-pulmonary medications** |
| Statins |
| Beta-blockers |
| ACE-inhibitors |
| ARBs |
| Calcium channel blockers |
| Thiazide-like and thiazide-type diuretics |
| Loop diuretics |
| Proton-pump inhibitors |
| H2-receptor blockers |
| Metformin |
| Sulfonylureas |
| SGLT2 inhibitors |
| DPP-4 inhibitors |
| GLP-1 receptor agonists |
| Benzodiazepines |
| SSRIs or SNRIs |

a. Our method for identifying respiratory antibiotics is described in Appendix Table 4, “Method for identifying respiratory antibiotics.

1. Outcome variable and study follow-up
   1. Outcome variables and study follow-up:

**Primary effectiveness outcome:** First moderate or severe COPD exacerbation

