**Secondary**

1. All-cause mortality
2. Annual rate of moderate or severe COPD exacerbations
3. Annual rate of moderate COPD exacerbations
4. Annual rate of severe COPD exacerbations
5. First moderate COPD exacerbation
6. First severe COPD exacerbation
7. Annual rate of hospitalizations for pneumonia
   1. Follow up and censoring

**Primary effectiveness and safety outcomes**: Follow up starts 1 day after the cohort entry date and continues until any of the following occurs:

(1) discontinuation of index therapy (with a 60-day grace period between fills and a 60-day exposure risk window)

(2) switch from exposure to referent or vice-versa

(3) initiation of a different inhaler regimen (ICS, LABA, ICS-LABA, LAMA-LABA, ICS-LABA-LABA)

(4) death

(5) the end of insurance coverage

(6) the end of data

(7) 365 days

1. **Statistical analysis**: For our primary balancing methodology, we will perform inverse probability of treatment weighting (IPTW) with stabilized weights using propensity scores estimated from an over-identified covariate balancing propensity score (CBPS) model. We specified a logistic regression model for the CBPS estimation procedure, including the variables in Table 1 as predictors of exposure.

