CBPS augments standard GLM propensity score estimation by imposing additional balance constraints, optimizing the likelihood function while iteratively “nudging” coefficient estimates toward a model that maximizes covariate balance between groups.^6,7^ This method has been shown to offer increased robustness to propensity score model misspecification, improved covariate balance in observational data, and reduced bias in estimating treatment effects compared to logistic regression, while still maintaining its ease of interpretability.^6,8^ IPTW is a standard method for estimating the average treatment effect (ATE), and the use of stabilized weights can offer increased precision.^9–11^ Furthermore, we found that CBPS-IPTW performed the best in our particular dataset in terms of achieving strong balance while avoiding extreme weights that could bias our estimates.^12^ This balance assessment is summarized in Table 2, which compares several methods on a set of important balance metrics.^7,13,14^ While entropy weighting outperformed in several important balance metrics, it made less efficient use of the data with a lower effective sample size (ESS) in the exposure group and also had extremely large weights that could bias our estimates. Several other metrics were also computed for both the main effect and higher order terms, such as the maximum standardized mean difference (SMD), the maximum Kolmogorov-Smirnov (KS) for higher order terms, the number of variance ratios greater than 0.5 and less than 2, the number of SMDs for higher order terms that exceeded 0.1, and finally, the ESS, weight ratio, and coefficient of variability (CV) for the referent group. However, these metrics were comparable between all the methods, and were therefore excluded from Table 2.

**
[figure not shown]
**

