To estimate the relative average treatment effect (ATE) on our time-to-event outcomes (including the primary effectiveness and safety outcomes, as well as our secondary outcomes of moderate COPD exacerbation and severe COPD exacerbation), we will estimate marginal hazard ratios (HRs) using Cox proportional hazards models of the respective outcome with the treatment as the sole predictor and incorporating balancing weights from CBPS-IPTW.^10,12^ The corresponding 95% confidence intervals will be estimated using cluster-robust standard errors (SEs).^12^ To estimate the ATE on annual rates of recurrent time-to-event outcomes (our secondary outcomes of annual rates of COPD exacerbations and pneumonia hospitalizations), we will use a Prentice, Williams, and Peterson Total Time Model in the weighted cohort, with a 14-day washout period after each exacerbation. This modified version of the Cox model does not assume constant baseline risk or independence between recurrent outcomes for a given individual, which is consistent with what we know about the increasing risk of subsequent COPD exacerbations.^15–19^ We will report both unadjusted and adjusted results for primary and secondary outcomes. In addition to hazard ratios, we will present the number of outcomes, mean duration of follow up, and reasons for censoring stratified by exposure. We will also produce adjusted cumulative incidence curves for both primary outcomes.^20,21^

1. **Subgroup analyses**

|  | **Subgroup*** | **Why?** | **Strengths** | **Weaknesses** |
| --- | --- | --- | --- | --- |
| **1** | 1 or more baseline moderate or severe COPD exacerbations | ICS-based regimens are thought to be especially valuable for those who frequently exacerbate. This subgroup analysis seeks to examine the comparative effectiveness of Advair Diskus and HFA in this population where ICS-based regimens are thought to be particularly beneficial. | Addresses comparative effectiveness and safety in high-risk patients | None |
| **2** | 1 or more baseline COPD hospitalizations | ICS-based regimens are thought to be especially valuable for those who frequently exacerbate. This subgroup analysis seeks to examine the comparative effectiveness of Advair Diskus and HFA in this population where ICS-based regimens are thought to be particularly beneficial. | Addresses comparative effectiveness and safety in high-risk patients | Low power |

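### The cluster-robust interval for the weighted Cox model ignores that the weights are estimated, so the primary effectiveness CI is usually somewhat too wide

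*Protocol*

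**What the plan says.** The rule comes from three places in the Protocol.

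- **Covariates.** Of Table 1 the text says "All variables listed below will be included in our propensity score model". The table lists baseline moderate and severe exacerbations, "Total COPD exacerbations (moderate or severe)", and exacerbations within 30 days of cohort entry.
- **Statistical analysis, weights.** Stabilized weights come from "propensity scores estimated from an over-identified covariate balancing propensity score (CBPS) model", a logistic model "including the variables in Table 1 as predictors of exposure". The section adds that "the use of stabilized weights can offer increased precision".
- **Statistical analysis, outcome model.** For the time-to-event outcomes, "we will estimate marginal hazard ratios (HRs)" from "Cox proportional hazards models of the respective outcome with the treatment as the sole predictor and incorporating balancing weights from CBPS-IPTW". Then: "The corresponding 95% confidence intervals will be estimated using cluster-robust standard errors (SEs)".

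No bootstrap or other allowance for weight estimation is named. For the recurrent-event (Prentice, Williams and Peterson) models no SE method is stated.

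**The concern.** Exacerbation history is a baseline measure of the primary effectiveness outcome, and it reaches the primary analysis only through the weights. When weights are estimated from covariates that predict the outcome, chance imbalance in those covariates is removed, and the sampling variance of the weighted log hazard ratio falls. A sandwich SE with fixed weights does not see this. It estimates roughly the variance the estimator would have if the true propensity scores had been used.

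The study asks whether two devices delivering the same drug combination differ, so interval width governs what it can conclude. An inflated SE can hide a modest difference and weakens any statement that the devices are similar. Efficiency is also one of the plan's own criteria: entropy weighting was set aside partly because of its lower effective sample size. Several subgroups are labelled low power.

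**Working it through.** **Inputs.** The Protocol fixes the estimator and the SE. It states no SE, sample size, event rate, exposure share or power, so there is no figure to reproduce. Every numerical input below is an assumption.

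**Mechanism.** Let φ be a patient's influence on the log hazard ratio with known weights, and S the score vector of the propensity model. With weights from a maximum-likelihood logistic model, the large-sample variance is

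Var(φ) − Cov(φ,S) Var(S)⁻¹ Cov(S,φ) ≤ Var(φ).

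The fixed-weight sandwich estimates Var(φ). The subtracted term grows with the prognostic strength of the covariates.

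**Simulation A.** N = 5,000, 15% on HFA, true HR 1, logistic propensity score, one prognostic confounder plus five noise covariates, one-year cap, 2,500 replicates. The ratio is the mean robust SE over the empirical SD of the log HR.

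| Scenario | Empirical SD | Robust SE | Ratio |
|---|---|---|---|
| log HR 0.3 per SD, 32-34% events | 0.0718 | 0.0713 | 0.99 |
| log HR 0.5 per SD, 32-34% events | 0.0681 | 0.0703 | 1.03 |
| log HR 0.8 per SD, 32-34% events | 0.0622 | 0.0685 | 1.10 |
| log HR 0.8 per SD, about 52% events | 0.0489 | 0.0562 | 1.15 |
| Rare outcome (as pneumonia), about 5% events | 0.1624 | 0.1646 | 1.01 |

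Monte Carlo error of an empirical SD is about 1/√(2 × 2,500) = 1.4%, so the first and last rows cannot be told from 1. Robust coverage was 94.7-97.8%.

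**Simulation B.** 30 scenarios, n = 8,000, 1,500 replicates each (Monte Carlo error about 2%), exposure 10%, 25% or 50%, events 16-59%, HR per baseline exacerbation 1.2, 1.4 or 1.8 with ten other covariates, again with a logistic propensity score.

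| Covariates | Robust SE / empirical SD, range | Mean of 10 scenarios |
|---|---|---|
| Weak | 0.96-1.02 | 1.00 |
| Moderate | 0.98-1.09 | 1.04 |
| Strong | 1.03-1.21 | 1.12 |

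Robust coverage was 94.3-98.1%. The empirical SD with estimated weights never exceeded that with known weights, and was at most 1 − 0.0248/0.0303 = 18% lower. The estimator therefore does receive the gain.

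**Simulation C.** Just-identified CBPS weights, n = 3,000 and 10,000, 10-15% exposed, about 33% events, at least 1,200 replicates. Robust over true SE was about 1.01-1.09, with coverage of about 95-97%. A bootstrap that re-estimated the weights gave SEs near the true SE.

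**What the ratios mean.** If power is 80% with the inflated SE, crediting the weights gives Φ(2.8016 × ratio − 1.96):

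- ratio 1.03: Φ(0.926) = 82%
- ratio 1.10: Φ(1.122) = 87%
- ratio 1.15: Φ(1.262) = 90%

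At an estimated HR of 1, the log HR 0.8 row with 32-34% events gives exp(±1.96 × 0.0685) = 0.87-1.14 as reported, against exp(±1.96 × 0.0622) = 0.89-1.13. In variance terms, 1.10² = 1.21, which is like giving up 1 − 1/1.21 = 17% of the information. For 1.03 the loss is 1 − 1/1.03² = 6%.

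**The case against.** The strongest reply is that the cluster-robust SE is an accepted choice, supported in the plan by a methods citation, and that its error is conservative. It neither biases the hazard ratio nor, as a rule, inflates false positives. The plan sets no equivalence margin or precision target that the extra width would defeat. The 10-15% excess needs a log HR of about 0.8 per SD (HR about 2.2), which nothing in the Protocol supports. With weak covariates there is no excess, and with 10% exposed and strong selection the ratio fell to 0.96-0.98. All of this stands and limits the size of the point.

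The simulations are also stand-ins. None used over-identified CBPS or the full Table 1 list, and neither the recurrent-event models nor the subgroups were simulated. In the strata without baseline exacerbations that covariate is constant and can contribute nothing. An analytic correction is not clearly safer either: it covered 93.0-94.5% with 10% exposed and strong selection.

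It could further be said that the Protocol never states that the weights are treated as known, and that such detail belongs in an SAP that is not shown. This carries less weight. The Protocol names the variance method, and a standard cluster-robust SE works that way.

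A reader might infer that the precision available from baseline adjustment is lost. The stated estimator does not support that: weighting on estimated scores retains the gain, and only the interval omits it. A reader might also infer that exacerbation history belongs in the Cox model. Because the hazard ratio is non-collapsible, that would replace the stated marginal target with a conditional one.

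**Conclusion.** The point holds as a modest matter of efficiency. For the primary effectiveness outcome the stated interval is usually somewhat too wide. Under the assumed inputs the SE excess is about 0% with weak covariates, about 3-5% with moderate ones and about 10% or more with strong ones. For pneumonia it is about 1%, within simulation error. The plan treats the risk of further exacerbations as rising after each one, which supports the direction but does not establish the strong-covariate case.

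It would go too far to say that the interval is always too wide or that the primary analysis is invalid. The documents give none of the quantities needed for the first, and the second does not follow from an error that is mostly conservative. The change is still worth making because it is cheap and leaves the estimate and the estimand as they are.

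**What to change.** In the Statistical analysis section, base the 95% CIs of the primary Cox models on a patient-level bootstrap. Each resample re-estimates the CBPS weights and refits the weighted treatment-only model. Use at least 1,000 resamples, because a percentile interval from few resamples can slightly under-cover, and state in advance whether the interval uses percentiles or the bootstrap SE. Keep the cluster-robust CI as a supplementary figure. Add no covariates to the Cox model.

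Apply the same bootstrap to the weighted recurrent-event and subgroup models for consistency, without claiming a gain there that has not been shown. Where a subgroup has few exposed patients and strong selection, slight under-coverage is possible, so report both intervals side by side.

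The cost is a sentence or two of analysis text and computing time. No new data are needed, and the point estimate and marginal hazard ratio are unchanged.

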Moderate COPD exacerbations are defined as requiring prednisone for 5-14 days, and severe COPD exacerbations are defined as requiring hospitalization (with COPD in the primary position). The full codes for moderate exacerbations, severe exacerbations, and moderate or severe exacerbations are below. Defining moderate exacerbations based on prednisone fills (of 5-14 days) has been validated with PPV of 0.73 (0.70-0.77).^3^ Note that, on sensitivity analysis, we will require both a prednisone and an antibiotic fill (PPV 0.80 [95% CI 0.74-0.86]).^3^ Defining severe COPD exacerbations based on COPD diagnosis codes in the primary position has been validated with a PPV of 0.86.^4^

The primary analysis is time to first moderate or severe COPD exacerbation. In secondary analyses (see below), we will analyze cumulative exacerbations during one year of follow up using a Prenctice, Williams, and Peterson Total Time Model. We will require that distinct episodes of exacerbation be separated by at least 14 days. Therefore, if a patient meets the criteria for an exacerbation more than once within 14 days, this will be counted as 1 unique episode that begins at the first exacerbation within the episode.

Episodes that meet both moderate and severe exacerbation criteria within 14 days of each other will be counted as 1 severe exacerbation that begins at the time of meeting the criteria for the first exacerbation within the episode, regardless of whether the criteria are for a moderate or severe exacerbation.

Therefore, there are 2 types of prednisone fills that would otherwise meet criteria for moderate exacerbations but are instead grouped as severe COPD exacerbations: (1) First, prednisone fills that occurred within 14 days AFTER the end of a COPD hospitalization will count as a severe COPD exacerbation beginning with the start of the COPD hospitalization. The prednisone script is likely just completing the therapy that was begun in the hospital and so should not count as a new exacerbation. (2) Second, prednisone scripts that occurred within 14 days BEFORE the start of a COPD hospitalization will count as a severe COPD exacerbation beginning with the start of the prednisone script. When prednisone is not enough and hospitalization is required, this episode is a severe exacerbation.

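### The Prentice-Williams-Peterson total-time model is said to estimate the treatment effect on annual rates, but it returns a hazard ratio conditional on earlier events, and no adjusted annual rate or rate ratio is planned.

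*Protocol*

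**What the plan says.** The Protocol's list of secondary outcomes contains four annual rates: "Annual rate of moderate or severe COPD exacerbations" (item 2), the same for moderate and for severe exacerbations separately (items 3 and 4), and pneumonia hospitalizations (item 7). The outcome definitions that precede section 8.1.A describe the exacerbation target as a one-year total: "we will analyze cumulative exacerbations during one year of follow up".

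The Statistical analysis section names the target, "To estimate the ATE on annual rates of recurrent time-to-event outcomes", and then the estimator: "we will use a Prentice, Williams, and Peterson Total Time Model in the weighted cohort, with a 14-day washout period after each exacerbation". Its reasons are that "This modified version of the Cox model does not assume constant baseline risk or independence between recurrent outcomes for a given individual", which it calls "consistent with what we know about the increasing risk of subsequent COPD exacerbations".

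On reporting, it states "In addition to hazard ratios, we will present the number of outcomes, mean duration of follow up, and reasons for censoring stratified by exposure". Neither the main analysis nor the sensitivity table contains a rate model, a weighted annualised rate or a mean cumulative count.

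**The concern.** An annual rate, or a cumulative count over a year, is a marginal quantity: the expected number of events per patient-year under each device, whatever each patient's history. The Prentice-Williams-Peterson (PWP) total-time model stratifies by event number. A patient enters stratum k only after k−1 events in follow-up, so the pooled coefficient compares devices among patients with equal post-baseline history. The weights come from covariates measured up to cohort entry and do not turn that conditional comparison into a marginal rate ratio.

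The stated reasons do not require this model. A marginal mean-rate model leaves the baseline rate unspecified and handles within-patient dependence through a patient-clustered robust variance.

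At stake is the reading of four secondary outcomes. A reader told that the result is the effect on annual rates would take a conditional hazard ratio for a rate ratio and, where the devices differ, would probably understate the difference in total burden.

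**Working it through.** The Protocol gives no event rate, expected effect or sample size for these outcomes, so there is no planned figure to reproduce. All inputs below are assumptions, except the 14-day separation of episodes and the 365-day limit.

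**1. What each model targets.** Let a patient's event rate be Z·r·λ0(t), where Z is a gamma frailty with mean 1 and variance θ, r = 0.80 in one arm and 1 in the other, and Λ0(t) is the cumulative baseline rate. Ignore the 14-day gap for the moment.

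- Mean rate: E[Z]·r·λ0(t) = r·λ0(t). The ratio of arms is r = 0.80 at all times.
- Rate given k−1 earlier events by time t: r·λ0(t)·{1 + θ(k−1)} / {1 + θ·r·Λ0(t)}. The ratio of arms is HR(t) = r·{1 + θΛ0(t)} / {1 + θ·r·Λ0(t)}.

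The term in k cancels. The hazard ratio is the same in every event stratum, including the first, and drifts from 0.80 at the start of follow-up towards 1. At one year:

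- 0.8 per year, θ = 1: 0.80 × 1.8 / 1.64 = 0.878
- 1.5 per year, θ = 2: 0.80 × 4.0 / 3.4 = 0.941
- 0.15 per year, θ = 1: 0.80 × 1.15 / 1.12 = 0.821

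A fitted PWP coefficient averages this drift over the year, so it falls between 0.80 and these values.

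**2. Simulation.** Each scenario had 400,000 patients allocated 1:1, up to one year of follow-up, a 14-day gap after each event and an effect of 0.80 on the individual hazard. Multiplier means the factor applied to a patient's hazard after the first event. Results without drop-out:

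| Rate/yr | θ | Multiplier | PWP | Mean-rate model | First-event Cox |
|---|---|---|---|---|---|
| 0.8 | 0 | 1 | 0.799 | 0.799 | 0.798 |
| 0.8 | 0.5 | 1 | 0.821 | 0.796 | 0.815 |
| 0.8 | 1 | 1 | 0.833 | 0.793 | 0.827 |
| 0.8 | 2 | 1 | 0.865 | 0.803 | 0.855 |
| 1.5 | 0.5 | 1 | 0.839 | 0.802 | 0.835 |
| 1.5 | 1 | 1 | 0.868 | 0.813 | 0.858 |
| 1.5 | 2 | 1 | 0.892 | 0.813 | 0.881 |
| 0.8 | 0 | 2 | 0.798 | 0.770 | 0.800 |
| 1.5 | 1 | 1.5 | 0.870 | 0.792 | 0.852 |
| 0.15 | 1 | 1 | 0.827 | 0.818 | 0.826 |
| 0.15 | 2 | 1 | 0.800 | 0.779 | 0.798 |

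With exponential drop-out at 2 per year, the frailty scenarios without event dependence gave PWP 0.821 to 0.870 and the mean-rate model 0.800 to 0.812. Under no effect, both models gave about 1.00. Monte Carlo error is about 0.01 or less in most scenarios.

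**3. Where the gap comes from.** In the frailty rows, PWP sits close to the first-event hazard ratio: 0.892 − 0.881 = 0.011, and 0.870 − 0.852 = 0.018 with event dependence added. PWP is slightly nearer 1 because later strata contribute events later in the year, when HR(t) has drifted further. With event dependence and no frailty, PWP recovers the individual hazard ratio (0.798), but the rate ratio is 0.770. A prevented first event also prevents the raised risk that would follow it, and conditioning on history leaves that part out.

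**4. Event-triggered censoring.** In a second simulation (600,000 patients per scenario), patients had an assumed 40% chance of leaving follow-up after each event. With θ = 2, the mean-rate model gave 0.834 at 0.8 per year (PWP 0.862) and 0.851 at 1.5 per year (PWP 0.884). It then closes only part of the gap to 0.80: (0.862 − 0.834) / (0.862 − 0.80) = 45%, and (0.884 − 0.851) / (0.884 − 0.80) = 39%.

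**The case against.** PWP is an established recurrent-event model, chosen here for a stated reason, event dependence. First-event analyses are planned alongside it, and crude rates could be derived from the promised event counts and mean follow-up. The SAP is not shown and might add annualised rates. All of this stands, except that it does not repair the mismatch: the Protocol itself names both the target and the estimator, and crude rates are unadjusted.

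Four stronger readings are tempting, and the documents do not support them.

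- A reader might infer that stratifying on post-baseline events, with baseline-only weights, causes most of the attenuation. The first-event Cox model shows nearly the same attenuation in the same data, so most of it is general to hazard ratios under frailty. The primary analyses share it.
- A reader might infer that every device difference on all four outcomes is materially shrunk. Without heterogeneity or event dependence there is no gap, and at 0.15 events per year it is about 0.00 to 0.02.
- A reader might infer a built-in push towards declaring the devices similar. The aims are to compare. The Protocol sets no equivalence margin or decision rule, and there is no bias under no effect.
- A reader might take the strata to be formed by on-treatment events. The censoring list is headed for the primary outcomes only, so the documents support no more than post-baseline events.

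The mean-rate model has its own requirement, censoring independent of event history. If the censoring list also applies to these outcomes, a switch or a new inhaler regimen could follow an exacerbation and breach it.

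**Conclusion.** The mismatch is certain and does not depend on any simulated number: the planned coefficient is a hazard ratio conditional on event history, it is labelled as the effect on annual rates, and no adjusted rate or rate ratio is planned for the four outcomes.

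The size is conditional on assumptions. With 0.8 to 1.5 events per year, frailty variance 0.5 to 2 and non-informative censoring, a true 20% reduction would show as roughly 18% down to 11%, against about 18% to 20% from a mean-rate model. The direction follows from the Protocol's own premise of rising risk after each exacerbation. Only secondary outcomes are affected, and PWP remains a valid answer to a conditional question. The change should be made, but it does not threaten the primary results.

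**What to change.** For secondary outcomes 2 to 4 and 7, make the main analysis a marginal mean-rate model (Lin-Wei-Yang-Ying: Andersen-Gill estimating equations) with the planned covariate-balancing weights and a patient-clustered robust variance. Report the rate ratio with weighted annualised rates per arm. Keep the PWP total-time model as a supplementary analysis, labelled as a hazard ratio conditional on the number of earlier events.

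State which censoring rules apply to the recurrent outcomes. Because the mean-rate model needs censoring unrelated to event history, also fit it on the one-year ITT follow-up that is already planned as sensitivity analysis 2, or add censoring weights if follow-up ends at a switch or a new inhaler regimen.

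The cost is a change of wording and one more model on the same start-stop data and weights, with no new data. The downside is the extra assumption about censoring, which the ITT run is there to probe.
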